### Recruitment

Recruitment will be conducted using flyers distributed to members of the Australian and New Zealand Critical Care Society (ANZICS) and Australian College of Critical Care Nurses (ACCCN). The target audience for recruitment will include critical care healthcare professionals within the organizational membership, who are then able to forward onto their networks and people who may not be members. The flyer will include a link to the study’s website containing further information about the trial and a registration form to be completed by interested participants.

### Informed consent

Those interested in participating will be able to register for the study through the study’s website (www.wellbeingandburnout.com) or through the distributed flyers. Additional information about the study (i.e. purpose, significance, study content, risks and benefits, and confidentiality principles) can also be accessed through the study’s website. Questions can also be asked through study website’s platform, as well as through emails, text messages, and phone calls. Participants that register for the study will be provided with an electronic version of the information sheet and consent form to be signed and returned prior to being accepted into the study.

### Group allocation and blinding

The project’s work group are experienced in research project management and will be responsible for the recruitment and intervention delivery in both intervention and active control groups. Randomization will be implemented using a randomization table created by a computer software, conducted by an independent research assistant who will be unaware of the characteristics of the study and will not have any involvement in the trial or access to the trial data. This will be a single-blinded study, where the outcomes of assessment will be blinded, however, participants will be aware of their group assignment. Members of the project’s work group that are involved in the assessment of participants will be blinded to the participant’s assignment. Additionally, since participants will have direct access to their intervention, participants will not be blinded to their group allocation, but will not know which intervention group is active.

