#### Active control group

The informal peer debrief will include mutual support between participants with shared experiences. Like PPSP debrief, its goals are not to achieve debrief outcomes, rather, to encourage social interaction and engagement between participants—enabling a platform to discuss concerns, problems, and feelings [40]. The informal peer debrief will be a semi-structured, 6-week, group-based virtual, peer debrief intervention. Peer support leader(s) will conduct the sessions but will not provide active solutions. The list of semi-structured questions will be consistent in both intervention and control debrief groups with differences in the ‘Pre-briefing’, ‘Discovering’, and ‘Deepening’ sections; informal peer debrief will not include problem-solving approach (see Table 2).

**Table 2 pone.0285038.t002:** Debrief session layout.

Topic	Content
Introduction	• Introduction of the support leader and researcher present in the session • What this study is about and who is conducting the study
**Pre-briefing**	• Purpose of the debrief session and the role of the support leader in facilitating discussions and prompting self-reflection • Items that can be discussed (i.e., encounters/stressors at the workplace) • **Management of situations using problem-solving approaches and connecting new learnings into future situations.**
Defusing	• Encouraging participants to talk about how they feel when encountered with a stressful situation. • Allow reflection of their feelings and recapping the scenario
**Discovering**	• Allow other participants to reflect on the situation and provide their thoughts and ideas • Enable participants to explore any similar situations that they may have encountered. • **Support leader(s) may ask other participants on how they would approach the situation, their rationale, and potential future strategies. The support leader(s) can also offer their own mental model on problem-solving approaches to deal with the situation.**
**Deepening**	• **Reflection on what can be done in similar future situations.** • **Finding a relationship between the suggested strategy to other situations at work.**
Summary	• Recapping what was discussed in the session • Ending with one thing that can be taken away from the session and used in their workplace.

Note: The intervention group (PPSP debrief) will also use techniques stated in both ‘roman’ and ‘bold’ typeface, whereas the control group will follow techniques noted in ‘roman’ typeface only.

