### Measurements

Participants will complete self-reported questionnaire measures at four timepoints: baseline (T0), after treatment (T2), 1-month follow-up (T3), and 3-months follow-up (T4). Qualitative journal entry will be completed throughout treatment (T1)—the journal entry will include reflective questions for participants complete. Participants will additionally provide sociodemographic characteristics at T0 and treatment feedback (both through an online questionnaire and demi-structured interviews) at T2. Examples of sociodemographic characteristics will include gender, age, living status, citizenship, employment, qualifications, and family responsibilities. Audits of study screening, enrolment logs, attendance list to the consult and debrief sessions (intervention and active control), and study records (completion of the assessment measures at the five assessment points) will also be conducted.

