### Secondary outcomes

The secondary measures are directed to determine the impact of the intervention. Secondary outcome measured using self-reported questionnaire instruments, treatment feedback questionnaire, feedback semi-structured interviews, and journal entry. The journal entry question on ‘I feel burned out’ will measure the participant’s perception on burnout. The treatment feedback questionnaire and feedback semi-structured interviews that addresses questions surrounding benefits of the intervention and changes in participant’s viewpoints measures the impact of the intervention.

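### Outcome assessment is called blinded, but all seven effectiveness questionnaires are self-reported by participants who know their arm

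*Protocol article*

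**What the plan says.** On blinding, the Group allocation and blinding section of the protocol article makes three statements.

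- The overall claim: "This will be a single-blinded study, where the outcomes of assessment will be blinded, however, participants will be aware of their group assignment".
- Staff blinding covers those work-group members "that are involved in the assessment of participants will be blinded to the" allocation. The same section says that the work group as a whole "will be responsible for the recruitment and intervention delivery in both intervention and active control groups".
- Participants know their group, "but will not know which intervention group is active".

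On how outcomes are obtained, the Measurements section says: "Participants will complete self-reported questionnaire measures at four timepoints". These are baseline (T0), after treatment (T2), and 1 and 3 months' follow-up (T3, T4). The Secondary outcomes section adds: "Secondary outcome measured using self-reported questionnaire instruments, treatment feedback questionnaire, feedback semi-structured interviews, and journal entry". Under Data collection methods, the questionnaires go out as a survey link by email.

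On contact between staff and arms, the debrief layout in Table 2 begins with "Introduction of the support leader and researcher present in the session". Data collection methods has the research team email people who miss an Individualized Management Plan (IMP) consult or a debrief session. Only the intervention arm has the IMP consult.

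**The concern.** Blinded outcome assessment protects a result when someone other than the participant rates the outcome and does not know the arm. If the outcome is the participant's own rating and the participant knows the arm, blinding other people does not change how that rating is given. Here the ratings concern burnout, mood, engagement, turnover intention and problem-solving. Expectation can move such ratings, and it could favour the arm that receives more.

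The comparison carries weight in this plan. Hypothesis 3 in the Introduction is superiority over informal peer debrief. The Sample size estimation section sets the trial at 110 participants (55 per group) from the effectiveness aim. The Planned analysis section specifies between-group mixed models and bias-corrected Cohen's d for T0-T2, T0-T3 and T0-T4. The Discussion expects statistically significant benefit and says that the results will serve as preliminary data for a larger trial. If the report calls assessment blinded, readers and the planners of that trial will trust those effect sizes more than the design allows.

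**Working it through.** No figure is in dispute, so the check traces each outcome to the person who reports or rates it and asks whether staff blinding could act there.

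| Outcome | Source (section) | Who rates | Can staff blinding protect it? |
|---|---|---|---|
| UWES-9, TIS, MBI, PES, DASS-21, PSI, PANAS | Self-report by emailed link (Measurements; Secondary outcomes; Data collection methods) | Unblinded participant | No |
| Journals and feedback questionnaire | Participant's account, coded by researchers (User-perceived acceptability; Planned analysis) | Participant, then coder | Not the account itself; possibly the coding |
| Feedback interviews | One-to-one interview, coded by researchers (same sections) | Participant, interviewer, coder | Possibly, but the topic is the intervention received, so content will often reveal the arm |
| Recruitment, enrolment, attendance, completion | Audits, logs, attendance lists, study records (Measurements; Feasibility; Planned analysis) | Study records | Not self-reported, so the problem does not arise |

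**Step 1: extent.** All seven instruments fall in the first row. With three post-baseline timepoints (T2, T3, T4), 7 × 3 = 21 instrument-by-timepoint assessments feed the effectiveness analysis, and none has a rater other than the participant.

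**Step 2: the fallback masking.** The section relies on participants not knowing which group is active. Three features make this doubtful:

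- Only the intervention arm has a one-to-one consult with a psychologist (Intervention group).
- Only that arm's debrief contains the problem-solving items (Table 2 and its note).
- The comparator is itself named an active control, so it is unclear what the statement means.

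Against this, both arms receive a six-week, group-based virtual debrief run by peer support leaders, which narrows the visible difference.

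**Step 3: staff roles.** The work group delivers both interventions, and the blinded assessors are members of that group. A researcher is present in sessions, and the research team follows up missed IMP consults. These statements create a risk of unblinding. They do not say that the people who attend sessions or chase non-attenders are the people who assess.

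**Step 4: disclosure.** The Discussion names the choice of an active control as a limitation. Neither it nor the Planned analysis section mentions unblinded self-report.

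**The case against.** The strongest reply is that nobody is misled. The sentence that claims blinded assessment also says that participants know their group, and the questionnaires are plainly described as self-reported. The trial is a pilot with feasibility and acceptability as its primary aims, most of its analysis is descriptive, and effectiveness is labelled preliminary. The control arm's similar debrief format narrows the expectation gap.

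Much of this is fair and limits the consequence. It does not rescue the claim: a careful reader can work out that the questionnaires are not blind-assessed, but the plan states the opposite as a design property.

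A reader might also infer more than the document supports:

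- *That every outcome is affected.* Recruitment, enrolment, attendance and completion come from audits and logs.
- *That the researcher in the sessions breaks the blind.* The article limits blinding to members involved in assessment, who may be different people.
- *That no blinding is possible at all.* Coding of journals and transcripts, and data handling, could be done blind, although content may reveal the arm.
- *That silence on analyst blinding is an error.* This is commonly left to an analysis plan or full protocol, and neither is shown.
- *That the information sheet presents the arms unequally.* It is not shown.

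Acceptability data are opinions about the intervention received, so a lack of blinding is not in itself damaging to them.

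**Conclusion.** The statement is wrong as written for the seven self-reported instruments. For the hypothesis 3 comparison the trial does not have blinded outcome assessment, and the claim that participants cannot identify the active group is doubtful. The audit-based feasibility outcomes stand. Overlap between session staff and assessors is a risk to be clarified, not a shown contradiction.

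Neither the size nor the certainty of bias can be taken from the document. A direction favouring the intervention arm is plausible, on the assumption that participants expect more from the arm with the psychologist consult. The conclusion that staff blinding does not protect these outcomes needs no such assumption. It rests only on the participants completing the questionnaires themselves and knowing their arm, both of which the article states.

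**What to change.** 1. In Group allocation and blinding, state that the questionnaire outcomes are assessed by unblinded participants, and delete the blinded-assessment claim for them. Withdraw or explain the statement about not knowing which group is active.
2. Limit the remaining blinding claim to named staff roles that can be blinded and are separate from delivery: coding of journals and transcripts with arm removed where possible, and analysis with arms labelled A and B until the mixed-model results are final.
3. In the Discussion, list expectation bias from unblinded self-report as a limitation on hypothesis 3 and on the effect sizes carried to the larger trial.

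The sample size, visits and instruments do not change. The cost is some rewording, coded arm labels and removal of arm identifiers before coding. The trial's stated rigour will look less favourable.

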### Data collection methods

Baseline (questionnaire scale, sociodemographic, work-related information), journal entry, post-treatment feedback, post-intervention (questionnaire scales), and one- and three-months follow-up (questionnaire scales) assessments will be performed by sending a survey link to participant’s email. Participants will be able to complete the questionnaires on an electronic device, such as a computer, tablet, or smartphone. The questionnaires will be checked weekly after each delivery to ensure participant’s completion. Participants that do not complete the questionnaires within a specified time will be sent a reminder via email. Likewise, if participants do not attend their Individual Management Plan and/or debrief sessions, the research team will contact participants via email to join the session or to re-book into another session during the week. The feedback semi-structured interviews will be conducted by inviting participants to attend a virtual one-on-one semi-structured interview, which will be organized through email communication.

### Data management

All data files including consent forms, intervention materials, participant’s data, consult and debrief notes, questionnaire data, and journal entry data will be stored in the Flinders University managed on-site Enterprise Storage. After the last data collection timepoint (T4), any identifiable data will be de-identified and stored for five years after publication of the results. Following the required data storage period, all data will be securely destroyed. Deidentified research data will be made publicly when the study is completed and published. Feedback of the study outcomes will be provided to participants via a short summary of the research outcomes and a copy of the published research project.

### Data monitoring

A data monitoring committee is not necessary for this study as the planned intervention is short and we are not expecting any harms or adverse effects during the intervention. An independent Safety Officer (researcher who is independent from the study team) will monitor the participant’s safety (from participant recruitment to the end of intervention delivery), scientific integrity, study risks and benefits, and ethical conduct of the study. There are no serious adverse events expected, but there may be potential adverse events that could occur during the Individual Management Plan and debrief sessions such as negative emotional reactions and mild distress. If an adverse event were to occur, the safety officer will be notified immediately.

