## Abstract

Critical care healthcare professionals are at high risk in developing burnout and mental health disorders including depression, anxiety, and post-traumatic stress disorder. High demands and the lack of resources lead to decreased job performance and organizational commitment, low work engagement, and increases emotional exhaustion and feelings of loneliness. Peer support and problem-solving approaches demonstrate promising evidence as it targets workplace loneliness, emotional exhaustion, promotes work engagement, and supports adaptive coping behaviors. Tailoring of interventions have also shown to be effective in influencing attitudes and behavior changes, attending to the individual experience and specific needs of end-users. The purpose of this study is to assess the feasibility and user-perceived acceptability of a combined intervention (Individualized Management Plan (IMP) and Professional Problem-Solving Peer (PPSP) debrief) in critical care healthcare professionals. This protocol was registered in the Australian and New Zealand Clinical Trials Registry (ACTRN12622000749707p). A two-arm randomized controlled trial, with pre-post-follow-up repeated measures intergroup design with 1:1 allocation ratio to either 1) treatment group–IMP and PPSP debrief, or 2) active control group–informal peer debrief. The primary outcomes will be conducted by assessing the recruitment process enrolment, intervention delivery, data collection, completion of assessment measures, user engagement and satisfaction. The secondary outcomes will explore preliminary effectiveness of the intervention using self-reported questionnaire instruments from baseline to 3-months. This study will provide the interventions’ feasibility and acceptability data for critical care healthcare professionals and will be used to inform a future, large-scale trial testing efficacy.

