This study will combine the three concepts of peer support, problem-solving and tailoring to determine its effectiveness in improving wellbeing and engagement and decreasing burnout amongst critical care healthcare professionals. To the authors’ knowledge, there are no similar studies with the proposed intervention within the critical care workforce. Thus, the primary aim of this study is to test the feasibility and user-perceived acceptability of a combined Individual Management Plan (IMP) and Professional Problem-Solving Peer (PPSP) debrief in comparison to informal peer debrief. Specifically, the study will test the feasibility of the recruitment process, enrolment, intervention delivery, data collection, and completion of assessment measures in a sample of critical care healthcare professionals. User-perceived acceptability will be assessed using participant engagement to the intervention and user satisfaction. The secondary aim is to examine the preliminary effectiveness of the intervention on improving wellbeing, work engagement, and decreasing burnout. This study hypothesizes that the combined intervention will be (1) feasible (in terms of recruitment, enrolment, intervention delivery, and data collection, and completion of assessment measures), (2) acceptable in terms of participant engagement and user satisfaction, and (3) effective in improving wellbeing, engagement, and decreasing burnout symptoms than the informal peer debrief intervention at post-treatment and at the two follow-up periods (1 month and 3 months).

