Secondary outcome measures using questionnaires will be analyzed following the Intention to Treat (ITT). ANOVA or chi-square will be used to compare the sociodemographic data and baseline outcome measures (T0) [50]. Secondly, longitudinal changes (baseline, post-treatment, and 1 month and 3 months follow-up) and the differences between the two groups will be examined using mixed linear models as these models are more precise than the repeated measures of ANOVA [50]. Missing or incomplete data will be considered in the ITT analysis using maximum likelihood estimation method [50]. Effect sizes will be calculated using Cohen’s *d* (bias corrected) to represent the difference between Standard Mean Changes (MC) (T0-T2, T0-T3, T0-T4) [50]. Calculation of SMC in each group will be conducted, providing the *d* index of the general effect size from the differences between combined Individualized Management Plan (IMP) and Professional Problem-Solving Peer (PPSP) debrief vs. informal peer debrief [50]. After the data is analyzed, summary tables will be provided for all planned evaluations at pre-treatment (T0), post-treatment (T2), 1 month follow-up (T3), and 3 months follow-up (T4) [50]. Results will be reported as frequencies and descriptive statistics (mean, standard deviation, and percentages), summarizing the characteristics of the total sample and participants within each group [50].

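### The Safety Officer's participant-safety window closes when intervention delivery ends, although follow-up and the hypothesized benefit run to 3 months (minor point)

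*Protocol article*

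**What the plan says.** The Data monitoring section of the protocol article dispenses with a data monitoring committee because the intervention is short and no harm is expected while it runs. An independent Safety Officer is appointed instead. For participant safety, the officer's period is given in brackets: "from participant recruitment to the end of intervention delivery". The same sentence lists scientific integrity, risks and benefits, and ethical conduct, with no period attached to them.

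The section also says where trouble is foreseen: "there may be potential adverse events that could occur during the Individual Management Plan and debrief sessions", with negative emotional reactions and mild distress as examples. On reporting, it says: "If an adverse event were to occur, the safety officer will be notified immediately". That sentence carries no end date.

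The assessment schedule runs longer. Measurements sets the questionnaires at "baseline (T0), after treatment (T2), 1-month follow-up (T3), and 3-months follow-up (T4". The Introduction hypothesizes superiority "at post-treatment and at the two follow-up periods (1 month and 3 months", and Planned analysis models "longitudinal changes (baseline, post-treatment, and 1 month and 3 months follow-up". According to Data collection methods, "one- and three-months follow-up (questionnaire scales) assessments will be performed by sending a survey link" to the participant's email.

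**The concern.** A period for safety monitoring is normally at least as long as the period over which benefit is assessed. Here the article states an end point, and that end point comes before the last assessment. This is a boundary that the document sets, not a detail that a condensed article leaves to the full protocol. No other section extends the officer's participant-safety role to T3 or T4.

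Two things make follow-up relevant to safety. First, the Intervention group section has the psychologist advise participants to put the strategies to use in everyday life, so use of the intervention need not stop with the last session. Second, the scheduled contacts at T3 and T4 are emailed surveys, and the questionnaires that the article lists do not include an adverse event question. A late event would reach the officer only if someone chose to report it.

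What is at stake is modest: prompt notice of a late adverse event in an individual, and the completeness of the harm data that this pilot hands to the larger trial.

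**Working it through.** The article gives no figure for this gap, so there is none to reproduce. The check compares the stated window with the assessment schedule.

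**Inputs**
- End of the safety window: end of intervention delivery (Data monitoring).
- Delivery, intervention arm: 2 weeks of IMP followed by 6 weeks of PPSP debrief, so 2 + 6 = 8 weeks (Fig 1 legend).
- Delivery, control arm: 6 weeks of informal debrief (Active control group). Assumption: it starts at baseline, since the article gives no start time.
- Follow-up: T3 at 1 month and T4 at 3 months (Measurements). The origin of the count is not stated. The order T2, T3, T4 suggests the end of treatment. The Abstract's "using self-reported questionnaire instruments from baseline to 3-months" could be read as a count from baseline.
- Assumption: the window is read per participant.

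**Conversion**
- 1 month = 365.25 / 12 / 7 = 4.35 weeks.
- 3 months = 3 × 4.35 = 13.0 weeks.

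**T4 counted from the end of treatment**
- Time outside the window = 13.0 weeks in either arm.
- Share of time after baseline: intervention 13 / (8 + 13) = 13/21 = 62%; control 13 / (6 + 13) = 13/19 = 68%.
- T3 and T4 both fall outside the window.

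**T4 counted from baseline**
- Intervention: 13.0 − 8 = 5.0 weeks outside the window.
- Control: 13.0 − 6 = 7.0 weeks outside the window.
- T4 still falls outside the window.
- T3 would fall at 4.35 weeks, which is 8 − 4.35 = 3.65 weeks before delivery ends in the intervention arm and 6 − 4.35 = 1.65 weeks before it ends in the control arm. A follow-up visit inside treatment contradicts the order T2, T3, T4, so this reading is the less likely one.

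**Result.** T4 lies after the window on either reading, by 5 to 13 weeks, most plausibly 13. These figures count calendar time and say nothing about how many harms would occur.

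**The case against.** The strongest reply is that the window fits the risk. The foreseen adverse events belong to the sessions, and a window that covers recruitment to the last session covers them. After that, apart from the feedback interview at T2, participants only fill in online questionnaires. The strategies in question concern sleep, exercise and relaxation, and the article identifies no delayed harm from them. People scoring 37 or more on the IES-R are excluded at entry and offered a psychologist consult. All of this stands, and it is why the point is small.

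Three stronger readings are tempting, and the document supports none of them.
- *A reader might infer that all oversight stops when delivery ends.* It does not: immediate notification of adverse events has no stated end, nor do the officer's duties on integrity, risks and benefits, and ethical conduct.
- *A reader might infer a change from active to passive detection.* The article never calls the monitoring active and describes no ascertainment procedure even during delivery. Notification is the only route that it states at any stage.
- *A reader might infer that benefit is measured in follow-up and harm is not.* The DASS-21, the negative affect items of the PANAS and the emotional exhaustion scale of the MBI are among the questionnaires collected to T4, and the mixed models compare the arms over all timepoints. Worsening at group level is captured for as long as benefit is.

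It can also be said that changing the phrase alone would achieve little, because it adds no way of learning about late events. That is correct, and the remedy has to include one.

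What remains is that an explicit end point for participant-safety monitoring falls before the end of participation. That fit with expected events does not cover unexpected ones, in a pilot of a combination for which the authors know of no similar study in this workforce.

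**Conclusion.** The point holds as a minor one. The period that the article states for the Safety Officer's participant-safety monitoring is shorter than the period over which participants are followed and benefit is tested. The shortfall is about 13 weeks per participant if T4 is counted from the end of treatment, and about 5 to 7 weeks if it is counted from baseline. The lower figures rest on the 8-week and 6-week delivery periods and on control debriefs starting at baseline. All figures assume a per-participant window; if the window means the end of delivery across the whole trial, participants who enter early are partly covered.

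The consequence is limited to late adverse events in individuals and to the harm data that the pilot supplies. The power calculation and the planned comparisons stand as they are.

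**What to change.** - In Data monitoring, let the officer's participant-safety period run from recruitment to the last assessment (T4).
- Add one adverse event question to the online surveys already sent at T2, T3 and T4, worded identically in both arms, and pass positive answers to the Safety Officer.
- Tabulate adverse events by arm to T4.

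The cost is up to about 3 more months of the existing officer's time per participant, one more survey item and one more table. The existing outcome instruments and their timing stay the same.

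Review of individual DASS-21 scores is not part of this change. It is a separate decision for the clinical team and the ethics committees. If they adopt it, it should use the psychologist consult and referral route already described under Eligibility criteria, apply equally to both arms, and have referrals recorded by arm.
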